### **UNIFIED PD RATE SCALE (UPDRS) (PARTIAL)**

#### **III- MOTOR EXPLORATION**

##### **1. Spoken language**

0 = Normal.

1 = Slight loss of expression, diction, and/or voice volume.

2 = Monotonous, drawn-out, but understandable; moderate change.

3 = Change marked, difficult to understand.

4 = Unintelligible

##### **2. Facial expression**

0 = Normal

1 = Minimal hyponymy; could be normal ("poker player face")

2 = Slight but clearly abnormal decrease in facial expression.

3 = Moderate hyponymia; lips parted on some occasions.

4 = Fixed or mask-like face with severe or total loss of facial expression, lips parted  $\geq 0.6$  cm)

##### **3. Resting tremor**

0 = Absent

1 = Mild and infrequent

2 = Of small amplitude and continuous, or of moderate amplitude and intermittent occurrence.

3 = Of moderate amplitude and present almost continuously.

4 = Of marked amplitude and present almost continuously.

##### **4. Action or postural tremor of the hands:**

0 = Absent

1 = Light; present during the activity

2 = Of moderate amplitude, present during activity.

3 = Moderate amplitude, present when maintaining a posture as well as during activity.

4 = Of marked amplitude, it makes feeding difficult.

##### **5. Stiffness: (Assessed through passive mobilization of the major joints, with the patient seated and relaxed. Do not assess the cogwheel rigidity phenomenon).**

0 = Absent

1 = Slight sensation only perceived when activated by contralateral movements or other movements.

2 = Mild to moderate.

3 = Marked, but allows easy access to the maximum range of motion.

4 = Severe, the maximum range of motion is achieved with difficulty.

##### **6. Digital dexterity. (The patient taps their thumb against their index finger rapidly and successively with the greatest possible amplitude; each hand separately).**

0 = Normal

1 = Slightly slow and/or reduced amplitude.

2 = Moderate alteration. Clear and early fatigue. Movement may occasionally stop.

3 = Serious alteration. Frequent hesitation when initiating movement or pauses while performing the movement.

4 = You can only perform the exercise.

[figure not shown]

**7. Hand movements. (The patient opens and closes their hand rapidly and successively with the greatest possible amplitude; each hand separately).**

0 = Normal

1 = Slight slowness and/or reduction in amplitude.

2 = Moderate alteration. Clear and early fatigue. Movement may occasionally stop.

3 = Serious alteration. Frequent indecision in initiating movement or pauses while performing the movement.

4 = You can only perform the exercise.

**8. Rapid, alternating hand movements: (Pronation-supination movements, vertically or horizontally, with the greatest possible range of motion and both hands simultaneously).**

0 = Normal

1 = Mild slowness and/or reduction in amplitude

2 = Moderate alteration. Clear and early fatigue. Movement may occasionally stop.

3 = Serious alteration. Frequent hesitation when initiating movement or pauses while performing the movement.

4 = You can only perform the exercise.

**9. Leg agility: (The patient taps their heel against the ground in rapid succession, lifting the leg completely. The range of motion should be 7 to 8 cm.)**

0 = Normal

1 = Slight slowness and/or reduction in amplitude.

2 = Moderate alteration. Clear and early fatigue. Movement may occasionally stop.

3 = Serious alteration. Frequent hesitation when initiating movement or pauses while performing the movement.

4 = You can only perform the exercise.

**10. Getting up from a chair. (The patient attempts to stand up from a wooden or metal chair with a vertical backrest, keeping their arms crossed over their chest.)**

0 = Normal

1 = Slow or requires more than one attempt.

2 = Stand up using the arms of the chair for support.

3. Tends to fall backward and may try several times even if able to get up without help.

4 = Cannot get up from the chair without help.

**11. Posture**

0 = Erected normally.

1 = Not fully erect, slightly bent, can be normal in elderly people.

2 = Moderately stooped posture, clearly abnormal, may be leaning slightly to one side.

3 = Intensely stooped posture with kyphosis; may be moderately inclined to one side.

4 = Marked flexion with extreme postural alteration

**12. March**

0 = Normal

1. The gait is slow, the feet may drag, and the steps may be short, but there is no propulsion or festination.

2 = Walks with difficulty, but needs little or no help; there may be some festination, short steps, or propulsion.

3 = Severe gait disorder requiring assistance.

4. Marching is impossible, even with assistance.

**13. Postural stability (Observe the response to a sudden backward displacement, caused by a push on the shoulders, with the patient standing with eyes open and feet slightly apart. Warn the patient beforehand)**

0 = Normal

1 = Retropulsion, although recovery occurs without assistance.

2 = Absence of postural reflex; could have fallen if the evaluator had not prevented it.

3 = Very unstable; tendency to lose balance spontaneously.

4 = Unable to stand without assistance.

**14. Bradykinesia and hypokinesia. (Combination of slowness, indecisiveness, decreased arm swing, reduced range of motion, and general scarcity of movement).**

0 = Absent

1 = Minimal slowness, giving the movement a decisive character; this could be normal in some people. Amplitude possibly reduced.

2 = Mild degree of slowness and scarcity of movements; clearly abnormal. There may be a decrease in amplitude.

3 = Moderate slowness, poor movement, or reduced range of motion.

4 = Marked slowness and poverty of movement with reduced amplitude of movements.

|                                                             |
|-------------------------------------------------------------|
| - Hoehn and Yahr Disability Stages Scale (modified): |
|-------------------------------------------------------------|

|                                    |
|------------------------------------|
| 0: Absence of signs of the disease |
|------------------------------------|

|                        |
|------------------------|
| 1.0: Unilateral change |
|------------------------|

|                                                   |
|---------------------------------------------------|
| 1.5: Unilateral alteration with axial involvement |
|---------------------------------------------------|

|                                                     |
|-----------------------------------------------------|
| 2.0: Bilateral alteration, without balance deficit. |
|-----------------------------------------------------|

|                                                                |
|----------------------------------------------------------------|
| 2.5: Mild bilateral alteration with recovery in the push test. |
|----------------------------------------------------------------|

|                                                                                                |
|------------------------------------------------------------------------------------------------|
| 3.0: Mild to moderate bilateral alteration, some postural instability, physically independent. |
|------------------------------------------------------------------------------------------------|

|                                                                         |
|-------------------------------------------------------------------------|
| 4.0: Severe disability, still able to walk or stand without assistance. |
|-------------------------------------------------------------------------|

|                                                     |
|-----------------------------------------------------|
| 5.0: Confined to bed or wheelchair unless assisted. |
|-----------------------------------------------------|

H&Y Score: \_\_\_\_\_

**Walking speed test without a cane**(A measure after familiarization)

| Test order:                       | Time (s) | Speed (m/s) |
|-----------------------------------|----------|-------------|
| Automatically selected gear speed |          |             |
| Maximum driving speed             |          |             |

**Freezing episodes (complete cessation of movement followed by resumption)( )No (**

**) Yes** Number of episodes: \_\_\_\_\_

Freezing time: \_\_\_\_\_

**Number of stumbles (loss of balance with unassisted recovery):** \_\_\_\_\_

### Walking speed test with a cane(A measure after familiarization)

| Test order:                       | Time (s) | Speed (m/s) |
|-----------------------------------|----------|-------------|
| Automatically selected gear speed |          |             |
| Maximum driving speed             |          |             |

**Freezing episodes (complete cessation of movement followed by resumption)( )No ( ) Yes** Number of episodes: \_\_\_\_\_  
Freezing time: \_\_\_\_\_

**Number of stumbles (loss of balance with unassisted recovery):** \_\_\_\_\_

### Timed up and Go test - TUG without cane(a repetition after familiarization)

Test order: \_\_\_\_\_  
Time: \_\_\_\_\_ Mon  
Number of freezing episodes: \_\_\_\_\_  
Freezing time: \_\_\_\_\_  
Number of stumbles: \_\_\_\_\_

### Timed up and Go- TUG test with cane(a repetition after familiarization)

Test order: \_\_\_\_\_  
Time: \_\_\_\_\_ Mon  
Number of freezing episodes: \_\_\_\_\_  
Freezing time: \_\_\_\_\_  
Number of stumbles: \_\_\_\_\_

### Self-perception of health

**In general, would you say your health is:**

Excellent..... 1  
Very good..... 2  
Good..... 3  
Bad..... 4  
Very Bad..... 5

**Compared to a year ago, how would you rate your overall health now?**

Much better now than a year ago..... 1  
A little better now than a year ago..... 2  
Almost the same as a year ago..... 3  
A little worse now than a year ago..... 4  
Much worse now than a year ago.....5

**"Compared to other people your age, how would you say your health is:"**

1. ( ) Better 2. ( ) Same 3. ( ) Worse

### **FREEZE OF GEAR SCALE (FOGQ)**

1. **During your worst state you walk:**
  - 0 Normally
  - 1 Almost normally – a little slow.
  - 2 Slow but completely independent
  - 3 Do you need help or a walking aid?
  - 4 Unable to walk
  
2. **Are your difficulties walking affecting your activities of daily living or your independence?**
  - 0 Not at all
  - 1 A little
  - 2 Moderately
  - 3 Severely
  - 4 Unable to walk
  
3. **Do you feel like your feet are stuck to the ground while you walk, turn, or when you try to start walking (freezing)?**
  - 0 Never
  - 1 Very rarely – once a month
  - 2 Rarely – once a week
  - 3 Frequently – once a day
  - 4 Always – every time you walk
  
4. **How long does your worst freezing episode last?**
  - 0 It never happened
  - 1 1 to 2 seconds
  - 2 3 to 10 seconds
  - 3 11 to 30 seconds
  - 4 Unable to walk for more than 30 seconds.
  
5. **How long does your typical episode of hesitation to start walking (freezing) last?**  

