### **Participants**

Individuals diagnosed with PD will be recruited from the community in the city of Belo Horizonte, Minas Gerais, Brazil. Recruitment will be done through patient lists from other projects with the same population, as well as through outreach on social media, hospitals, primary health care units, and university spaces. Individuals who meet the following criteria will be included.: age  $\geq 40$  years; PD diagnosis confirmed by a neurologist; Classification of II to IV in the Hoehn & Yahr (HY) Disability Stages(GOULART et al., 2005) use of anti-Parkinsonian medication and medical stability for at least 6 months; ability to walk independently in a 14-meter corridor at a walking speed equal to or less than 1.1 m/s; ability to use a single-point cane correctly and safely

while walking without prior use of assistive devices. To assess the individual's ability to use the cane, the following criteria will be adopted: 1) absence of visual, cognitive, physical, or auditory impairment that prevents training and use of the device; and 2) absence of loss of balance while walking with the device.(KEGELMEYER et al., 2013; MCCANDLESS et al., 2016)Individuals with cognitive impairment, as assessed by the Mini-Mental State Examination.(BRUCKI et al., 2003)or that present any other neurological, cardiopulmonary, or musculoskeletal condition that may compromise the performance of the tests will be excluded.

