### **Procedures**

Individual assessments will be conducted at NEUROLAB/UFGM. Assessments will be conducted by a trained researcher blinded to group allocation. All assessed individuals will be informed of the study objectives and will sign the Informed Consent Form. During the initial assessment, eligibility criteria will be verified. For individuals who meet these criteria, sociodemographic data (sex, age, education, socioeconomic level, and occupation) and clinical data (disease duration and Unified PD Rating Scale (UPDRS)) will be collected.(GOULART et al., 2005)For the UPDRS scale, section III will be specifically evaluated, as it is used to assess the impact of the disease on the individual's motor function.(SHEARIN et al., 2021; GOULART et al., 2005).

The included participants will be randomly allocated to the experimental group or control group by the physiotherapist responsible for the intervention. This physiotherapist will be blinded to the assessment performed and previously trained on the intervention procedures. After allocation, individuals in the intervention group will be instructed to maintain their usual healthcare routines and they will receive training on how to use a cane. The training will be conducted at NEUROLAB, UFGM, whose approval has already been obtained, and will be offered in four 40-minute sessions spaced 15 to 22 days apart. In addition, they will be instructed to use the cane during their daily mobility activities, both indoors and outdoors, from the first day of training. To monitor adherence

to cane use, individuals will receive a diary to record their daily use of the device during mobility activities.

Individuals allocated to the control group will be instructed to maintain their usual health care routine and not start using any walking aids during the study period. To control the amount of attention received, individuals in the control group will receive a placebo intervention containing global stretching and health education. The intervention will be carried out at NEUROLAB, UFMG, and will be offered by the same physiotherapist responsible for training the experimental group in four 40-minute sessions spaced 15 to 22 days apart.

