### Freezing of gait

Freezing during gait will be assessed using the Gait Freezing Questionnaire (*Freezing of gait questionnaire*, FOG-Q). This questionnaire has six items whose objective is to evaluate freezing during gait in patients with PD (Baggio et al., 2012; Oliveira, 2010).The instrument has already been cross-culturally translated into Brazilian Portuguese (Baggio et al., 2012)Furthermore, the questionnaire has adequate measurement properties and is considered reliable for screening and measuring the severity of frostbite, as well as for evaluating this outcome after interventions. (Baggio et al., 2012)In addition to the questionnaire, the number and duration of freezing episodes that patients experience during the gait speed test and the TUG will be reported.

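### FOG-Q item 1 gives points for needing a walking aid, so assigning a cane to one arm can raise that arm's freezing total with no change in freezing

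*Combined protocol and SAP*

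**What the plan says.** The Freezing of gait section makes the FOG-Q the questionnaire measure of this secondary outcome: "This questionnaire has six items whose objective is to evaluate freezing during gait in patients with PD". Data analysis lists freezing of gait among the outcomes compared between groups by repeated measures ANOVA over baseline, post-training and follow-up. It gives no FOG-Q scoring rule and no special handling of any item.

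The form in Appendix II prints six items, each scored 0 to 4. Item 1 opens "During your worst state you walk". Its middle response is "2 Slow but completely independent" and the next one up is "3 Do you need help or a walking aid". Neither the stem nor the responses of item 1 mention freezing. Items 3 to 6 are the ones that ask about freezing or hesitation.

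Under Participants, entry requires "ability to walk independently in a 14-meter corridor at a walking speed equal to or less than 1.1 m/s" and cane ability "while walking without prior use of assistive devices". Under Procedures, the experimental arm is treated differently from its first session: "they will be instructed to use the cane during their daily mobility activities, both indoors and outdoors, from the first day of training". Controls are told not to take up a walking aid while in the study. Cane use continues between the two reassessments, so both post-baseline FOG-Q measurements fall in the period of cane use.

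The Gait speed, Functional mobility and Freezing of gait sections also provide for recording the number and duration of freezing episodes seen during the walking test and the TUG.

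**The concern.** One response category of the outcome questionnaire names the kind of device that the trial gives to one arm and withholds from the other. A cane user who now regards the cane as something they need can answer 3 on item 1 where they answered 0, 1 or 2 at baseline, with identical answers to every freezing item. No control is given the same reason to change.

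The resulting shift would run in one direction, against the cane, and a larger sample would not remove it. In the between-group comparison it could offset a real reduction in freezing or produce an apparent worsening. The plan does not say whether item 1 is to be answered with or without regard to the study cane, so participants may read it differently. Nor does it report the item separately, so a reader of the results could not tell an item 1 shift from a freezing effect.

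**Working it through.** The plan states no figure on this point, so there is none to reproduce. What can be checked is the score arithmetic.

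**Inputs from the documents.** Six items, each printed 0 to 4 (Appendix II); 13 participants per arm (Sample calculation); two-sided 5% level taken from the 5% in Data analysis.

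**Inputs not in the documents (assumptions).** The share of the experimental arm that moves to response 3; its baseline item 1 answers; the FOG-Q standard deviation, taken as 3 to 6 points.

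**Step 1, ranges.** Six-item total: 6 × 4 = 24. Without item 1 (items 2–6): 5 × 4 = 20. Freezing-specific items 3–6: 4 × 4 = 16. The 0–24 total is derived, since no scoring rule is given.

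**Step 2, change per person.** Moving to response 3 adds 3 − 2 = 1, 3 − 1 = 2 or 3 − 0 = 3 points. As a share of the total that is 1/24 = 4.2%, 2/24 = 8.3% or 3/24 = 12.5%. Someone already at 3 or 4 cannot be moved up to 3.

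**Step 3, mean artefact in the arm.** Mean artefact = share moving × points per mover.

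| Share of arm moving | 1 point each | 2 points each |
|---|---|---|
| 0% | 0 | 0 |
| 50% | 0.5 | 1.0 |
| 100% | 1.0 | 2.0 |

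The illustrative range is therefore 0 to 2 points.

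**Step 4, what such a shift does to a comparison.** The table gives the chance that a two-sample t-test at one visit, 13 per arm, is significant when the artefact is the only difference. This is simpler than the planned ANOVA and serves only to show scale.

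| Mean artefact | In SD units (SD 6 to SD 3) | Chance of p < 0.05 |
|---|---|---|
| 0 | 0 | 5% (nominal) |
| 0.5 | 0.08 to 0.17 | 5.5% to 6.9% |
| 1 | 0.17 to 0.33 | 6.9% to 12.9% |
| 2 | 0.33 to 0.67 | 12.9% to 37.2% |

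**Step 5, masking.** A true 2-point improvement would appear as 2 − 1 = 1 point with a mean artefact of 1, and as 2 − 2 = 0 with a mean artefact of 2.

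**Step 6, after the change.** With item 1 left out (items 2–6 or items 3–6), the item 1 artefact is 0 by construction.

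**The case against.** The strongest reply is that the item asks what the person needs, at worst, and not what they use. Everyone enrolled could walk independently at entry. A participant who carries a cane because the trial asked for it can quite properly keep answering 0, 1 or 2. This stands: the shift is possible, not automatic, and could be nil. The printed English is also visibly a rough translation, and the item turns on the exact Portuguese wording, which is not shown.

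Baseline scores may limit the effect too. Response 3 also covers help from others, Hoehn & Yahr stage IV is eligible, and entry walking is assessed in the medicated state while the item asks about the worst state. Some participants may already score 3 or 4. At the other end, the 1.1 m/s ceiling makes a baseline answer of 0, and so a 3-point jump, less likely for many. Both points stand and reduce the plausible size.

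It is also fair to say that the plan does not rely on the questionnaire alone. The episodes counted and timed in the walking test and TUG do not depend on item 1. They cover only brief supervised tests, however, whereas the FOG-Q asks about freezing more generally, so they help interpretation without replacing the questionnaire comparison.

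Finally, the six-item questionnaire is the instrument that the protocol describes as having adequate measurement properties, and nothing in the documents supports a subscore. That is a reason to keep the total, not a reason to leave item 1 unexamined.

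A reader might also infer that an answer of 3 tells the blinded assessor which arm the participant is in. The documents do not support that: the response equally means help from others, so a control can choose it.

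**Conclusion.** The point holds as a possible, one-directional bias in one secondary outcome. The documents establish the mechanism: item 1 does not ask about freezing, it gives 3 points for needing an aid, and the aid is assigned by randomisation. They do not establish its size. Per person it is 1 to 3 points of 24. For the arm mean, 0 to 2 points is an illustration that rests on an assumed 0 to 100% of the arm moving by 1 to 2 points, and the significance figures rest further on an assumed SD of 3 to 6.

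A reader might go further and conclude that the treatment is built into the score for every cane user, or that the trial's freezing results are unusable. Neither follows. The item's wording leaves room for no shift at all, and items 3 to 6 and the observed episodes do not depend on item 1. The primary outcome, gait speed, is unaffected. The change is worth making because it is cheap and is more credible if fixed before the data are seen.

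**What to change.** Add to Data analysis: the between-group FOG-Q comparison will be made both on the six-item total and on the score without item 1; item 1 will be tabulated by arm at each assessment; and a worse total in the experimental arm will not be interpreted as worse freezing unless the score without item 1 and the observed freezing episodes agree.

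Name the reduced score in advance. Items 2–6 (0–20) is the smallest change that removes the problem. Items 3–6 (0–16) is also defensible, but the plan should then say why item 2 is dropped as well, for example because it asks about walking difficulty and independence in general and not about freezing. The same section should state how the total is scored.

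The cost is a sentence or two, with the same questionnaire, visits and data. The small downside is that the reduced score is a subscore that the documents do not describe as validated, which is why the six-item total is reported beside it.

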**to take the first step)?**
  - 0 Nothing
  - 1 It takes more than 1 second to start walking.
  - 2 It takes more than 3 seconds to start walking.
  - 3 It takes more than 10 seconds to start walking.
  - 4 It takes more than 30 seconds to start walking.
  
6. **How long does your typical hesitation to turn last (freezing while turning)?**
  - 0 Nothing
  - 1 Around 1 to 2 seconds
  - 2 Around 3 to 10 seconds
  - 3 Around 11 to 30 seconds
  - 4 Unable to complete the turn for more than 30 seconds.

